## Abstract

**Background:**

The purpose of the Aging-ON_DUAL-TASK_ study is to determine if a supervised dual-task program carried out in long-term nursing homes is able to attenuate frailty in a greater extent than the same multicomponent exercise program alone.

**Methods:**

This multicenter randomized controlled trial will include 188 participants who will be randomly allocated to either a multicomponent exercise program or to the same multicomponent program with simultaneous cognitive training (dual-task training). Inclusion criteria are as follows: ≥ 70 years, ≥ 50 on the Barthel Index, ≥ 20 on the Mini Examen Cognoscitivo (MEC-35) who are able to stand up and walk independently for 10 m. Subjects in the multicomponent group will attend a twice-a-week multicomponent exercise program of 1-h duration per session, consisting of strength and balance exercises. Participants in the dual-task group will perform the same multicomponent exercise program with concurrent individually tailored cognitive tasks. Study assessments will be conducted at baseline and at 3 months. The primary outcome measure will be gait speed under dual-task conditions and secondary outcomes will include physical fitness measurements, gait spatiotemporal parameters, cognition and emotional assessments, several frailty scales and objectively measured physical activity.

**Discussion:**

The present research will add valuable information to the knowledge around the effects of the dual-task program in long-term nursing home residents, taking altogether physical, cognitive and emotional variables linked to frailty.

**Trial registration:**

Australian and New Zealand Clinical Trials Registry (ANZCTR) with the identifier: ACTRN12618000536268. Registration date: 11/04/2018.

## Introduction

The global increase in life expectancy and consequent aging of the population, leads to estimates that the number of dependent older adults will rise from 350 million in 2010 to 488 million by 2030 [1]. Accordingly, the number of older adults living in long-term nursing homes will also increase considerably. Older adults in long-term nursing homes represent a complex and heterogeneous population with a high prevalence of dependence in the activities of daily living, cognitive impairment, depression, high fall rates, multimorbidity and polymedication [2, 3]. In addition, long-term nursing home residents tend to be extremely inactive, engaging in sedentary activities for most of the day [4]. Thus, providing the best care for this population has become a challenge for both social and health care services [5].

In the last few years, research in aging has focused on frailty syndrome. Frailty is considered a state of vulnerability highly prevalent among the older adult population [6–8]. Although frailty has traditionally been described as a purely physical syndrome, a number of epidemiological studies have reported that frailty increases the risk of future cognitive decline and that cognitive impairment increases the risk of frailty, suggesting that physical frailty and cognitive impairment interact [9]. Cognition declines with age, with normal subtle cognitive changes that may affect everyday life functioning [10] and frail older adults usually perform worse in certain executive function and processing speed tests [11]. Recently, the International Academy on Nutrition and Aging (I.A.N.A) and the International Association of Gerontology and Geriatrics organized an International Consensus Group on “Cognitive Frailty”, which proposed a definition of cognitive frailty [12] and suggested that all frail older adults should undertake a complete cognitive evaluation, including executive function tests [13].

In consonance with this idea, an impaired capacity to perform attention-demanding mobility activities such as carrying out two tasks (physical + cognitive) simultaneously, also known as *dual-task*, could be a novel marker of physical and cognitive frailty. Many activities of daily life involve the performance of several tasks at a time, creating competing demands for attentional resources that challenge both motor and cognitive functions [14]. Considering that attentional capacity is limited, when demands exceed capacity, performance of dual-tasks can be affected compared to performance of the same tasks in a *single-task* fashion. Indeed, older adults show greater impairments compared to their younger counterparts in cognitive-motor dual-task performance, such as naming animals while walking or making calculations during balance exercises [15, 16]. Additionally, low dual-task performance capacity is associated with cognitive impairment and with a high risk of falling [17–19].

Previous studies of dual-task as a test of functional performance in older adults have focused on the gait speed test or on the Timed Up and Go test as physical tasks, while introducing semantic fluency or a calculus command as cognitive content. The difference between performance in the dual-task and the single-task tests is known as *dual-task interference* or *dual-task cost* [20]; this difference increases with aging [21]. The dual-task cost can be accounted for in both the physical and the cognitive domains. In this regard, the most commonly used formula is: dual-task cost = ((dual task − single task) single-task) × 100% [18]. For the physical dual-task cost calculation, time in seconds is used, whereas for the cognitive dual-task cost, either the number of correct responses or the percent of correct responses can be used to compare between single and dual task performances.

Dual-task performance can be modified with specific dual-task training [22, 23]. In fact, this type of intervention can maintain or even improve cognitive function [24, 25], especially executive function [26]. Two models have been suggested that might explain training-mediated dual-task performance changes [27]. The task-automatization model is based on the assumption that individual tasks can be automatized and predicts similar improvements either with single-task or dual-task training [27]. Alternatively, the task-integration model advocates for the efficient integration of both tasks through dual-task training, resulting in dual-task performance improvements [27]. According to the latter model, dual-task performance would only improve after dual-task but not single-task training. Furthermore, dual-task training may be superior to single-task training [28–30], since dual-task training requires greater cognitive and motor resources and is more complex in terms of control and coordination demands. Pellecchia et al. [31] observed greater improvements in postural sway under dual-task conditions after dual-task training compared to single-task training, supporting the task-integration model and suggesting that both physical and cognitive functions interact in a way still to be revealed.

To our knowledge, no studies have explored the effects of a supervised dual-task multicomponent exercise intervention in long-term nursing home facilities from a broad perspective of frailty, assessing functional capacity under single-task and dual-task conditions, physical activity, cognitive performance and emotional status. Therefore, we designed a randomized multicenter study, the Aging-ON_DUAL-TASK_ study, to test hypothesis that the addition of cognitive training to a supervised multicomponent exercise program can improve gait speed performance under dual-task conditions by, at least 0.08 m/seg in a population of older adults in long-term nursing homes. The major aim of the Aging-ON_DUAL-TASK_ study is to determine if a supervised dual-task program carried out in long-term nursing homes can attenuate frailty to a greater extent than the same multicomponent exercise program without cognitive training.

The Aging-ON_DUAL-TASK_ study is based on a previous study [32, 33] in which feasibility regarding recruitment, adherence and safety of the multicomponent exercise program were successfully ascertained. A pilot study was performed to refine the outcome assessments, establish the progression of the cognitive training, and optimize the organizational infrastructure.

## Methods

### Study design and participants

Based on the proposed objective, an experimental multicentre simple randomized study was designed (Aging-ON_DUAL-TASK_). Participants will be randomly allocated to either a multicomponent exercise program or to the same multicomponent program with simultaneous cognitive training (dual-task program). Participants will be recruited from eight long-term nursing homes in Gipuzkoa, Basque Country, Spain. Each site will enroll a minimum of 16 subjects and interventions will take place between June 2018 and December 2018. Researchers responsible for data gathering will be blinded to group assignment. The assessments will be carried out by research staff at baseline and at 3 months after the beginning of the intervention. The study has been designed and results will be reported following the CONSORT Statement extension for trials of non-pharmacological interventions and pragmatic intervention trials (Fig. 1).

**Fig. 1 Fig1:**
[figure not shown]
Flow diagram of the study

### Inclusion and exclusion criteria, recruitment, and randomization

The inclusion criteria, recruitment, and randomization methodologies in the Aging-ON_DUAL-TASK_ study will be the same as on a previously published protocol [33]. The inclusion criteria will be: age ≥ 70 years old; a Barthel Index [34] score ≥ 50 and score ≥ 20 on the MEC-35 Test [35] [Mini-examen cognoscitivo, an adapted and validated version of Mini Mental State Examination (MMSE) in Spanish]; and capacity to stand up and walk independently for at least 10 m. Participants will not be eligible if they are judged clinically unstable by the medical staff, or have in any other condition in which entering the study would not be in the subject’s best interests.

Identification of individuals that meet the inclusion criteria will be facilitated by the databases of the included long-term nursing homes. The primary recruitment strategy will be information provided to the potential participants by the medical and nursing professionals from each facility. All volunteers will receive detailed study information at their reference sites through the research team: objectives, measurement variables, and other details about the interventions will be explained orally and in writing to both potential participants and their families. After signing the informed consent, the participants within each center will randomly be assigned (in a 1:1 ratio) through sealed opaque envelopes to either the multicomponent or the dual-task group by coin-tossing sequence generation.

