Inhibition		If the instructor says *YES* they respond *NO* and viceversa	Every time the instructor says HEADS they have to answer TAILS and viceversa and Previous entry	If a green card is presented they have to say RED and when a red card is presented they have to say GREEN	Level 2 and level 3 instructions altogether	If the word RED is presented in a green color they have to say *GREEN* and vice versa and when the word YES in red color or NO in green color, they have to name the colo*r*.
Problem solving (calculus)		Counting by twos starting from a number ≥ 30	Counting by threes from a number ≥ 50	Substracting by twos from a number ≥ 30	Substracting by threes from a number ≥ 50	Substracting by fours from a number ≥ 100
Movement coordination		Inherent to the muticomponent exercise program				
Movement learning and sequencing						

The first week of the intervention will mainly serve to familiarize participants with the strength and balance exercises and adjust the level of difficulty of each cognitive function task to every participant in the group. In the second week, strength tests will be performed to individualize strength training and ensure training intensity. Throughout the following weeks, dual tasking will be applied mostly in strength exercises to train for divided attention allocation and will progressively move to balance exercises to optimize training adaptations and mimic everyday situations that require double tasking and increasing instability.

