### Power and sample size

Sample size for the current study was calculated to detect a significant clinical difference on the dual-task gait speed test [54]. Accepting an alpha risk of 0.05 and a beta risk of 0.20 in a bilateral contrast, 141 individuals are required to detect a difference equal to or greater than 0.08 m/seg in the dual-task gait speed test (SD = 0.24). The sample size was increased by 20% to account for losses during follow-up and an additional 5% for mortality. The resulting sample size is 188 individuals, allocating 94 participants to each group.

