### Statistical considerations

Data analysis will be performed using the IBM SPSS Statistics 24 statistical software package (SPSS, Inc., Chicago, IL). Intention-to-treat analyses will be performed and the level of statistical significance will be set at *p* < .05 for all computations. First, all data will be checked for normality of distribution using the Kolmogorov-Smirnov test. Results will be expressed as mean (with standard deviation) for continuous and normally distributed variables and as median (with interquartile range) when normality of data for that variable cannot be assumed. In the case of categorical variables, frequency counts and percentages will be used to describe the results. Tests for baseline comparisons will be selected based on the nature and distribution of the data: Student’s-t test with continuous and normally distributed variables, Mann-Whitney test with non-normally distributed continuous variables, and Chi-squared test with categorical variables.

To test the effects of training interventions, mixed-designed ANCOVA-s or the Friedman test, including baseline measurements, age, or gender as covariates, will be performed for physical, cognitive, and emotional variables. In cases where a significant F value is found, LSD post hoc procedures will be performed for pairwise comparisons.

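### Residents are allocated within each of eight homes, but the stated model leaves home out and makes adjustment for the outcome's own baseline optional, so the primary analysis is not fixed and gives up precision

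*Protocol article*

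**What the plan says.** In the protocol article, the section on inclusion criteria, recruitment and randomization states that "the participants within each center will randomly be assigned (in a 1:1 ratio) through sealed opaque envelopes", with the sequence generated by tossing a coin. The section on study design and participants gives eight nursing homes and calls the design simply randomised. No block or other restriction is mentioned.

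The section on statistical considerations offers a mixed-design ANCOVA or the Friedman test for the training effects, "including baseline measurements, age, or gender as covariates". No term for home appears there.

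The sample-size section works with "Accepting an alpha risk of 0.05 and a beta risk of 0.20 in a bilateral contrast" and states that "141 individuals are required to detect a difference equal to or greater than 0.08 m/seg" "in the dual-task gait speed test (SD = 0.24"). The number was then "increased by 20% to account for losses during follow-up and an additional 5% for mortality", giving 188. It makes no allowance for home or for the correlation between baseline and follow-up.

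**The concern.** Two things are badly fixed in one sentence of the statistical section.

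- **Baseline.** The baseline value of the outcome is usually the strongest predictor of its 3-month value. Joined by *or* to age and gender, it becomes one option among three. One sentence thus permits several different primary analyses, with different standard errors.
- **Home.** Allocation takes place inside each home, and homes may differ in their residents' gait speed. Leaving home out puts that variation into the residual.

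The Friedman alternative makes the first problem worse. It takes no covariates, and it tests repeated measures within subjects rather than comparing the arms. On that route neither the adjustment nor the trial's own comparison can be carried out.

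At stake are the precision of the primary comparison and the assurance that it was settled in advance.

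**Working it through.** **Inputs from the article:** two-sided alpha 0.05, power 0.80, difference 0.08 m/s, SD 0.24 m/s, 141 evaluable in total (70.5 per arm), eight homes. **Assumed, because not given:** baseline to 3-month correlation r of 0.5 to 0.8, and between-home ICC of 0.02 to 0.20. The article does not say whether 0.24 is the SD of the endpoint or of the change. It is taken as the endpoint SD unless stated.

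**The plan's own figure.** n per arm = 2 × [0.24 × (1.960 + 0.842) / 0.08]² = 141.28. So 141 reproduces as a per-arm number, while the article uses it as the trial total (141 / 0.75 = 188). That is a separate matter. Here 70.5 per arm is used because it is what the plan expects to have.

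**Baseline adjustment.** SE with no baseline = 0.24 × √(2/70.5) = 0.0404. Power ≈ Φ(0.08/SE − 1.960). The variance is multiplied by 2(1 − r) for a change analysis and by 1 − r² for ANCOVA.

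At r = 0.7:

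- no baseline: 0.08/0.0404 = 1.98, power 0.51 (0.50 with the t distribution)
- change: variance × 0.60, SE 0.0313, power 0.72
- ANCOVA: variance × 0.51, SE 0.0289, power 0.79

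| assumed r | no baseline | change | ANCOVA |
|---|---|---|---|
| 0.5 | 0.51 | 0.51 | 0.63 |
| 0.6 | 0.51 | 0.60 | 0.70 |
| 0.7 | 0.51 | 0.72 | 0.79 |
| 0.8 | 0.51 | 0.88 | 0.91 |

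If 0.24 were instead the SD of the change, the change analysis would have power 0.51. ANCOVA would multiply its variance by (1 − r²)/[2(1 − r)] = (1 + r)/2 = 0.85 at r = 0.7, so SE = 0.0404 × √0.85 = 0.0373 and power is about 0.57.

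**Home.** If the arms are exactly balanced within home, a model without home overstates the SE by 1/√(1 − ICC): 1.0%, 2.6%, 5.4% and 11.8% at ICC 0.02, 0.05, 0.10 and 0.20. Adjusting for home alone, with no baseline, raises power from 0.51 to 0.52, 0.53, 0.55 and 0.60.

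A simulation of 8 homes with 18 evaluable residents each (8,000 replicates, Monte Carlo error about 0.0024) gave these type I error rates for the model without home:

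| assumed home ICC | unrestricted coin toss | exact 1:1 within home |
|---|---|---|
| 0.05 | 0.049 | 0.047 |
| 0.10 | 0.050 | 0.040 |
| 0.20 | 0.051 | 0.032 |

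The test is valid in the first case and conservative in the second. In neither is it too liberal.

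**The case against.** **The named model already uses baseline.** With two assessments, a mixed-design ANCOVA most naturally has time as the within-subject factor, and its time-by-group test is a change analysis. A reader might infer from the *or* that the trial drops from 79% to 50% power. The article does not support that: 50% belongs to a post-only comparison which it does not name. The realistic loss at r = 0.7 is 72% against 79%. In a change analysis a time-constant home effect also cancels, so the gain from a home term is smaller than shown above. This objection stands, and it limits the size of the point.

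**Omitting home and the error bars.** A reader might infer that ignoring the allocation stratum makes the intervals too narrow. It does not, as the simulation shows.

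**Shared training classes.** A reader might also infer that residents trained together in one home and arm are correlated, so that the test is too liberal. With an assumed class ICC of 0.02 to 0.05 and 141/16 ≈ 8.8 per class, the design effect would be 1.16 to 1.39 and a nominal 5% test would run at about 7 to 10%. In simulation a home main effect did not cure this. But the article gives neither class composition nor class size nor an ICC. Its nearest phrase, "adjust the level of difficulty of each cognitive function task to every participant in the group", concerns tailoring of tasks, and the group there may simply mean the arm. This supports a conditional sensitivity analysis and no more.

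**Covariates picked after seeing baseline tests.** The article plans baseline significance tests but nowhere links them to the choice of covariates.

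**The analysis plan may settle it.** A centre term could well be in a fuller plan, and its absence alone would not be a finding. The article, however, does not defer the covariates: it states a list, and that list is worded so that the analysis is not determined.

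**Conclusion.** The point holds as one of unfixed wording and lost precision. Home is missing from a stated covariate list although allocation is within home, and adjustment for the outcome's own baseline is optional.

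Most of the gain comes from baseline: about 7 percentage points of power over a change analysis at an assumed r of 0.7 (79% against 72%), with ANCOVA power between 0.63 and 0.91 for r of 0.5 to 0.8. These figures rest on 0.24 being the endpoint SD and on 141 evaluable residents in total. The home term adds little, and its omission is at worst mildly conservative for ICC 0.02 to 0.10. The documents do not show that the type I error is inflated.

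Which of the two home cases applies cannot be settled from the article, because a coin toss does not guarantee the 1:1 ratio that it states within each centre.

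**What to change.** - Pre-specify one primary model: ANCOVA of 3-month dual-task gait speed on arm, always adjusted for its baseline value, age, gender and home (an eight-level factor). Replace *or* with *and*.
- Use the same model for the other continuous outcomes, each with its own baseline value.
- Do not substitute the Friedman test when normality is in doubt.
- State whether allocation was restricted within home, and if so how.
- If sessions are delivered in classes formed by home and arm, say so, and add a sensitivity analysis of the primary outcome with a random class term and small-sample degrees of freedom.

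The cost is a change of wording, seven degrees of freedom for home out of 141 evaluable residents, and possibly a slightly wider interval in the sensitivity analysis. No new data are needed.

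### Unrestricted coin tossing secures neither balance within nursing homes nor 94 per arm; use a computer-generated list blocked and stratified by home, and adjust for home

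*Protocol article*

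**What the plan says.** Three sections of the protocol article bear on allocation.

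- **Study design and participants:** "an experimental multicentre simple randomized study was designed". There are eight homes, and "Each site will enroll a minimum of 16 subjects".
- **Inclusion and exclusion criteria, recruitment, and randomization:** once a resident has consented, allocation is made separately in each home, 1:1, with opaque sealed envelopes, "to either the multicomponent or the dual-task group by coin-tossing sequence generation". The same section says that the "randomization methodologies in the Aging-ON_DUAL-TASK_ study will be the same as on a previously published protocol", which is not available here.
- **Power and sample size:** "The resulting sample size is 188 individuals, allocating 94 participants to each group".

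No section mentions blocks, a separate list for each home, minimization or any other restriction. The article does not say who tosses the coin, when, or whether the results are written down. Statistical considerations names baseline measurements, age or gender as covariates for the effect analyses. Home is not among them.

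**The concern.** Independent tosses give each resident a 50% chance of either programme and take no account of the home or of the running totals. If 1:1 within each centre is only a statement of probability, the words about the centre add nothing. If it is meant as balance inside each home, the stated method does not secure it. The reader cannot tell which is intended, and the same doubt attaches to 94 per group.

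With eight small sites, simple randomization will often leave a marked imbalance in at least one. Residents in both arms keep the usual activities of their home, and these may differ between homes. Any chance association between arm and home is then handled neither by the design nor by the covariates named for the analysis. Finally, a tossed sequence cannot be reproduced from a seed if the allocation is later questioned.

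**Working it through.** **Inputs from the article.** Total 188; 94 per group; eight homes; at least 16 per home; two-sided alpha 0.05; beta 0.20; difference 0.08 m/s; SD 0.24. The average home size is 188/8 = 23.5.

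**The plan's own figure.** 141/(1 − 0.25) = 188, and 188/2 = 94. So 94 is half the inflated total.

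**Arm sizes overall.** Under coin tossing, the size of one arm is Binomial(188, 0.5).

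- P(94:94) = C(188, 94)/2^188 = 0.058.
- SD of an arm size = √188/2 = 6.9.
- The central 95% range is 81 to 107 (probability 0.951).
- P(99:89 or worse) = 0.51; P(104:84 or worse) = 0.17.

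**Splits within homes.** The article gives no sizes beyond the minimum, so near-equal homes are an assumption. An event is a home in which the larger group is at least twice the smaller.

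| Assumed home sizes | Chance in one home | Chance in at least one of eight |
|---|---|---|
| Eight of 24 (16:8 or worse) | 0.152 | 1 − (1 − 0.152)^8 = 0.73 |
| Eight of 23 (16:7 or worse) | 0.093 | 1 − (1 − 0.093)^8 = 0.54 |
| Four of 23, four of 24 (total 188) | 0.093 and 0.152 | 1 − (0.907^4 × 0.848^4) = 0.65 |

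Eight homes of 24 total 192, slightly above 188. The result moves with home size because counts are whole numbers, but such a split somewhere is more likely than not in every row.

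**Power cost of unequal arms.** Power = Φ(0.08/(0.24·√(1/n1 + 1/n2)) − 1.96).

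- 94:94 gives Φ(2.285 − 1.96) = 62.75%.
- 107:81 gives Φ(2.263 − 1.96) = 61.9%.
- The cost at the edge of the 95% range is about 0.8 points. Averaged over coin tossing, power is 62.5%.

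The level is about 63% rather than 80% because, on these inputs, 141 is what the formula gives per arm, while the article uses it as the total. That is a separate matter and does not change the comparison. Relative efficiency at 107:81 is 4 × 107 × 81/188² = 0.981. A design with 80% power at equal arms would fall to Φ(2.802 × √0.981 − 1.96) = 79.2%, again less than 1 point.

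**Under restriction, for illustration.** With permuted blocks of four within each home, the difference is at most 2 per home, so at most 8 × 2 = 16 overall (102:86), and usually much less.

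**The case against.** The strongest reply is that nothing here is invalid. A 1:1 ratio ordinarily means equal probability, which a fair coin delivers. Simple randomization and coin tossing agree with each other, and 94 per group reads naturally as half the planned total. All of this stands. A reader might infer that the method cannot deliver 1:1, or that the sections describe incompatible schemes. The text does not support that: what is missing is a guarantee.

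A reader might also infer that the sequence cannot be audited, or that unwelcome tosses could be repeated. The article does not support that either. Tosses made in advance can be logged and sealed, the envelopes are opaque and sealed, data gatherers are blinded, and randomization details are deferred to an earlier protocol. What remains is that tosses cannot be regenerated and that no record is described.

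The consequences are also limited. Chance imbalance by home adds variance but does not bias the comparison, and a 16:8 split still leaves both arms represented in that home. The article gives no between-home variance, so the size of any home effect is unknown. It gives no class-size limit, so a claim that a programme could not run as planned has no basis. Assuming eight homes of exactly 16 would raise the chance of an 11:5 or worse split somewhere to 85%, but that describes 8 × 16 = 128 participants, not 188, and should not be used.

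The deferral does not remove the point. The article states this trial's method itself, so this is a stated choice and not an omitted detail.

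**Conclusion.** The point holds as an inexpensive improvement to a valid method. As written, the plan secures neither balance within homes nor 94 per arm. Exactly 94:94 has probability 5.8%, and one arm may plausibly number anywhere from 81 to 107. With eight homes of about 24, at least one split of 16:8 or worse has probability about 73%. Over the near-equal home sizes shown, the chance of a 2:1 or worse split somewhere runs from 54% to 73%. These figures assume independent fair tosses and near-equal homes.

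The overall arm sizes matter little, since the power loss is under 1 percentage point. The reasons to act are chance imbalance by home, with home absent from the named covariates, and a sequence that cannot be regenerated. How much home matters for dual-task gait speed cannot be judged from the article.

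**What to change.** 1. Replace coin tossing with a computer-generated list in permuted blocks of randomly varying size, stratified by home. Someone not involved in recruitment or assessment should generate it before enrolment and archive it with its seed.
2. Keep the sealed opaque envelopes.
3. In Study design and participants, replace simple randomized with randomized, stratified by home.
4. In Power and sample size, describe 94 per group as the target.
5. In Statistical considerations, include home as a factor in the primary model, so that the analysis follows the stratified design.

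The cost is under an hour of a statistician's time. The one drawback is slight predictability at the ends of blocks, which is limited by varying the block sizes at random and concealing them from the homes. If allocation has already begun, leave it as it is, report the splits by home, adjust for home, and state who generated the sequence and how it was recorded.
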